### Assignment of interventions: allocation and blinding

Due to the nature of the intervention, participating physicians and hospitals cannot be blinded to their assignment. The principal investigator (PI) and study statisticians will not be blinded to the group allocations. The trial biostatistician will be blinded to the data analyses. The diagnostic testing intervention and the de-escalation intervention, delivered as clinical decision support, will be implemented at the intervention hospitals, limited to participating physicians. To ensure balanced study arms concerning hospital type, we will conduct stratified randomization. Hospitals will be grouped into three strata as described previously. A senior statistician in the Department of Quantitative Health Sciences will program the cluster randomization procedure using STATA 17 MP. The *ralloc* procedure allocates two treatments, called Rx1 and Rx2, to 12 hospitals in three strata using a 2 × 2 factorial design. Blocks of equal frequency allocate treatments labeled “Rx1” and “Rx2” equally in each of the three strata. A random seed was set by the trial statistician and kept hidden. In each stratum, hospitals are arranged in alphabetical order.

### Data collection and quality check

The period of data accrual for each patient will be for 6 months from the time of admission. Data will be extracted from the EMR by the data scientist periodically. Data collection will include patient demographics and characteristics, associated comorbidities, diagnostic and other laboratory tests, antibiotic prescribing data, and the primary and secondary outcomes. A data analyst will extract the data from electronic medical records at both intervention and control hospitals and a statistical programmer will review it for completeness and accuracy. Data will be coded using standardized codes and stored in a secure, password-protected database with regular backups. Any data inconsistencies will be verified by cross-referencing the original medical records. Missing, incorrect, or out-of-range values will be addressed. Routine internal audits of the database will be conducted by the research team.

## Statistical methods

### Data analysis plan

The data analysis will be conducted following the intention-to-treat (ITT) principle which includes 3 rules. The first rule establishes the landmark event for entry into the study, which is the randomization of hospitals. All randomized hospitals will be considered enrolled, and data of eligible patients treated by enrolled hospitals will be analyzed. The second rule establishes patient-level data collection, which is independent of treatment assignment. The third rule defines the pre-specified time period for counting study events, which varies for each outcome.

We will follow the order principle of analyses, which states that analyses involving the primary outcome measure must be preceded by analyses of higher-order outcomes when those outcomes are censored. In our study, all-cause death events are censored. To follow the order principle of analyses, we will compare the all-cause mortality incidence rate within the first 30 days of admission across the four treatment groups. Incidence rate is calculated as the number of all-cause deaths divided by the number of included patients and expressed per 1000 (or 10,000 patients) per 30 days of follow-up. We will calculate the incidence-rate difference between the four treatment groups, using the usual care group as the reference. The four treatment arms are rapid testing and de-escalation, rapid testing only, de-escalation only, and usual care (i.e., neither rapid testing nor de-escalation).

The primary outcome of days on ESA will be analyzed using a linear mixed-effects model, which will include the treatment arm as a fixed effect and a random-intercept at the randomized hospital level. We will adjust for baseline covariates between the intervention and control groups. These covariates include patient age, sex, race, CURB65, Elixhauser index, serum Na, serum glucose, hemoglobin, MRSA nasal swab (yes/no), WBC count, albumin, baseline oxygenation for CAP patients (O_2_ sat off O_2_ or supplemental oxygen delivery device type (vent > bipap > high flow, etc.), max or median respiratory rate on day 1, min SBP on day 1, vasopressors, and comorbidities (chronic pulmonary disease, lymphoma, metastatic cancer, obesity), as well as hospital characteristics in the year prior to study initiation (duration of antibiotics and ESA, AKI, CDI, 14-day mortality, and 30-day mortality, all among CAP patients who would have met study criteria). The primary comparison is to compare the duration of exposure to ESA therapy in the four treatment groups. Interaction between the two interventions will be tested as a secondary analysis. We will consider a two-sided *p*-value < 0.05 statistically significant. As we use a priori stratification (by the type of hospital), we will examine differential intervention effects by each pre-defined stratum. The primary outcome data will be available for every patient since it is recorded in the EHR. In case of missing secondary data, we will assume it is missing at random and a sensitivity analysis will be performed with data imputed via Multiple Imputation by Chained Equations (MICE).

To address the non-adherence limitation, we will conduct two secondary analyses [17]. First, we will perform an as-treated analysis, comparing outcomes among those who receive the treatment versus those who receive control, regardless of randomization. Second, we will calculate complier average causal effect (CACE) estimation, which uses randomization as an instrument to account for unobserved confounding and provides a randomization-respecting estimate [18]. CACE estimates the intention-to-treat effect in the subgroup of participants who always comply with their treatment allocation. In addition, we will use per-protocol analysis, comparing those who comply with their random allocation in the treatment group with all the controls. We will use an inverse probability weighting approach to minimize selection bias [19]. All the secondary analyses will use the framework of mixed-effects (hierarchical, two-level) models as described above for the primary ITT analyses.

All continuous secondary outcomes will be analyzed using the same method as the primary outcome. For each secondary outcome, we will adjust for the rate of that outcome in the 12 months prior to the study. Binary outcomes will be analyzed using generalized linear mixed-effects models. All analyses will be conducted using SAS 9.3 (Cary, NC), R-studio (Boston, MA), and STATA (College Station, TX). Our trial will follow the Consolidated Standards of Reporting Trials guidelines, extended for cluster-randomized controlled trials [20].

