### Participating sites

Enrolling sites will include ten hospitals in Northeast Ohio (Cleveland Clinic Main Campus, Fairview Hospital, Hillcrest Hospital, Marymount Hospital, Akron General Hospital, Avon Hospital, Euclid Hospital, Lutheran Hospital, Medina Hospital, and South Pointe Hospital) and two from Florida (Weston and Indian River Hospital) (Table 2). Hospitals will be divided into 3 strata based on teaching status, size of the hospital, and number of CAP patients with each stratum containing 4 hospitals. The hospitals will then be randomized to each of the 4 trial arms with an effective sample size of 3 hospitals in each arm.

**Table 2 Tab2:** Enrolling hospital sites by bed size and teaching status

Hospital	Number of beds	Residency program
Cleveland Clinic Main Campus	1167	Yes
Fairview General Hospital	488	Yes
Hillcrest Hospital	341	No
Marymount Hospital	195	No
Akron General	532	Yes
Avon Hospital	126	No
Euclid Hospital	110	No
Lutheran Hospital	119	Yes
Medina Hospital	148	No
South Pointe Hospital	167	Yes
Cleveland Clinic Florida, Weston Hospital	230	Yes
Indian River Hospital	332	No

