### Sample size and power analysis

The sample size calculations were based upon the primary outcome of reduction exposure to ESA. For Aim 1, we anticipate an average reduction of 0.3 days (SD = 3.5 days) of exposure to ESAs due to rapid diagnostic testing, based on our preliminary data. To achieve 83% power to detect this effect size at a two-sided alpha of 0.05 and an intra-cluster correlation (ICC) of 0.001, we will randomize 12 hospitals (6 in the rapid diagnostic testing arm and 6 in the control arm) with an average of 1000 patients per hospital (coefficient of variation (COV) = 0.4). This will result in a total sample size of 12,000 patients (6000 patients per arm).

For Aim 2, we will compare the six hospitals implementing pharmacist-led antimicrobial de-escalation and the other six hospitals serving as the control group. De-escalation is expected to reduce exposure to ESAs by 1 day (SD = 3), based on our preliminary data. Assuming a 50% compliance rate in the de-escalation arm, we will have > 99% power to detect this effect size at a two-sided alpha of 0.05 and an ICC of 0.005. We will also have > 99% power to detect a reduction in the rates of CDI from 1 to 0.5% and AKI from 6 to 3%, under the same assumptions. Since testing the interaction is a secondary analysis, power calculation was not performed. All power calculations were conducted using PASS 14 (Kaysville, UT).

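### Six hospital-level covariates on 12 randomised hospitals leave 2 or 3 degrees of freedom, so the primary model cannot deliver the stated 83% power for Aim 1

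*Protocol article*

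**What the plan says.** Under Data analysis plan, days on ESA are analysed with a linear mixed model, "which will include the treatment arm as a fixed effect and a random-intercept at the randomized hospital level". The model is adjusted for a list of patient covariates and for "hospital characteristics in the year prior to study initiation (duration of antibiotics and ESA, AKI, CDI, 14-day mortality, and 30-day mortality". These rates are taken from CAP admissions that would have been eligible for the trial. That makes six hospital-level measures: antibiotic duration, ESA duration, AKI, CDI, 14-day mortality and 30-day mortality. The primary comparison is described as one between the four treatment groups, and the interaction is secondary.

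Under Sample size and power analysis, Aim 1 assumes "an average reduction of 0.3 days" with an SD of 3.5 days. The target is put this way: "To achieve 83% power to detect this effect size at a two-sided alpha of 0.05 and an intra-cluster correlation (ICC) of 0.001". It is to be met with 12 hospitals, six on each side of the testing factor, whose sizes average 1000 patients and vary with a coefficient of 0.4. No allowance for covariates is mentioned.

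Under Participating sites, hospitals are stratified on teaching status, "size of the hospital, and number of CAP patients with each stratum containing 4 hospitals". In the analysis the strata appear only in this sentence: "As we use a priori stratification (by the type of hospital), we will examine differential intervention effects by each pre-defined stratum". They are not listed as a term in the primary model. No degrees-of-freedom method is named.

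**The concern.** Both interventions vary only between hospitals, so the treatment effect is estimated from 12 independent units however many patients are enrolled. Patient-level covariates cost almost nothing in this respect. Each hospital-level covariate costs one of the few hospital-level degrees of freedom. With 12 units, six such covariates will also correlate with arm by chance, which inflates the standard error of the treatment effect.

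The power statement and the analysis model therefore describe different analyses. If the model is fitted as written with t-based inference, a true 0.3-day effect would more likely be missed than found. If a normal critical value is used instead, the type I error exceeds 5%.

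**Working it through.** **Inputs (Sample size and power analysis):** effect 0.3 days, SD 3.5, ICC 0.001, two-sided alpha 0.05, 6 versus 6 hospitals, mean 1000 patients per hospital, coefficient of variation 0.4, 6000 patients per side.

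**Step 1: reproduce the 83%.**
- Design effect = 1 + ((1 + CV²)m − 1) × ICC = 1 + (1.16 × 1000 − 1) × 0.001 = 2.159.
- SE = 3.5 × √(2 × 2.159/6000) = 0.0939, and 0.3/0.0939 = 3.195.
- Noncentral t on 12 − 2 = 10 df (critical value 2.23): power 82.1%.
- With the relative-efficiency correction for unequal cluster sizes, the design effect is 2.082, SE is 0.0922 and power is 83.4%.
- With a normal critical value, power is 89.2% or 90.2%, which does not match.

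The stated figure thus corresponds to an unadjusted comparison on 10 hospital-level df.

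**Step 2: count hospital-level parameters in the stated model.**
- Four arms: 12 − (1 + 3 + 6) = 2 df, critical t 4.30.
- Two factor indicators: 12 − (1 + 2 + 6) = 3 df, critical t 3.18.

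**Step 3: change the df only, holding the SE at its planned value.** This assumes covariates exactly balanced across arms that explain nothing. The ranges cover the two design effects.
- 3 df: power 58–60%.
- 2 df: power 42–43%.

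**Step 4: allow for chance correlation with arm.** I simulated hospital means with 20,000 trials per scenario, equal hospital sizes and six independent random hospital covariates. The between-hospital variance is 0.001 × 12.25 = 0.01225 and the sampling variance of a hospital mean is 12.25/1000 = 0.01225. Without covariates the SE is √(0.0245 × 4/12) = 0.090. All rows test the 6-versus-6 factor effect with t-based inference.

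| Model | df | Median SE | Power |
|---|---|---|---|
| Two factors, no hospital covariates | 9 | 0.090 | 84% |
| Two factors + six, uninformative | 3 | 0.146 | 31% |
| Two factors + six, one explains half the between-hospital variance | 3 | 0.126 | about 38% |
| Two factors + six, one explains 90% | 3 | 0.108 | 47% |
| Two factors + strata + one, uninformative | 6 | 0.094 | 73% |
| Two factors + strata + one, explains half | 6 | 0.081 | about 83% |

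In the second row, power would be only about 53% even if the variances were known exactly and no df penalty applied. Much of the loss is therefore SE inflation, which no df method removes. In the fifth row, holding the SE at its planned value gives 76–77% on 6 df.

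**Step 5: type I error if a Wald z test were used.** With six uninformative covariates it is about 9% (two factors) to 10% (four arms) at ICC 0.001. At ICC 0.005, the value assumed for Aim 2, it is about 13–14% and 16%. With no hospital covariates and ICC 0.001 it is already about 7%, so part of the excess comes from having only 12 clusters.

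**The case against.** The best defence is that hospital-level adjustment can help. Prior-year ESA duration should predict trial-period ESA use, and the other rates may stand in for case mix. This is fair, and it is why the 31% should be read as the uninformative end of a range. It does not rescue the stated power. With 3 df, exact balance and the larger design effect, covariates explaining 90% of the between-hospital variance give 82.9%, and chance correlation with arm lowers that to 47%. With 2 df, even covariates that explain all of it with exact balance give 68%. The sound objection to the other five measures is their number, not that they are irrelevant.

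A second defence is that the df method may sit in an analysis plan that is not shown. That is also fair, so the type I error figures are conditional on a z test being used. The covariate list, however, is fixed in this article, and a small-sample method would repair the error rate without restoring power.

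Three stronger readings are tempting but not supported:
- **That omitting the strata causes the power loss.** It does not. Adding two stratum terms to four arms and six covariates gives 12 parameters for 12 hospitals and 0 df. The omission is a separate mismatch between design and analysis.
- **That power falls from 83% to 13%.** The 13% belongs to a single-arm contrast of 3 versus 3 hospitals, which has only 54% power with no covariates at all. It is not comparable with a 6-versus-6 figure.
- **That the protocol plans inestimable four-arm effects within each stratum.** There would be one hospital per cell, but the text speaks only of differential intervention effects by stratum. Factor-by-stratum effects fit those words and can be estimated on 3 hospital-level df.

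**Conclusion.** The point holds for Aim 1. The primary model leaves 2 or 3 hospital-level df, while the 83% rests on 10. On a like-for-like 6-versus-6 contrast with two factors, power falls from 84% to between 31% and 47%, depending on how much between-hospital variance one of the six covariates explains (none to 90%). On the df change alone it is 58–60% or 42–43%. The simulated figures assume equal hospital sizes, covariates that are independent of each other and unrelated to arm except by chance, and the protocol's SD and ICC. Inflated type I error is a risk only if a normal-based test is used. The plan also powers 6-versus-6 factor effects but names a four-group comparison as primary, and that needs to be settled for any power figure to have a clear meaning.

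**What to change.** Amend the Data analysis plan before any unblinded analysis:

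1. Keep prior-year ESA duration among CAP patients as the only hospital-level covariate in the ESA model, and drop the other five. The article already says that each secondary outcome is adjusted for its own rate in the 12 months before the study, so this narrower approach is consistent with it. Patient-level covariates are not affected by this point.
2. State that the two 6-versus-6 factor effects are the primary contrasts. This changes the stated four-group comparison and should be declared as such. Single-arm contrasts against usual care rest on 3 versus 3 hospitals and would be supportive.
3. Test with a small-sample df method such as Kenward-Roger or Satterthwaite.
4. Separately, add the randomisation strata as two terms once the list is cut, leaving 12 − (1 + 2 + 2 + 1) = 6 df. Report stratum results as factor-by-stratum estimates or descriptively.
5. Restate Aim 1 power for that model: about 72–77% if the retained covariate is uninformative, and about 83% if it explains half the between-hospital variance.

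The cost is a change of wording and less adjustment for chance hospital differences on the dropped measures. The restated power may also fall below 83%, and this should be reported openly.

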### Objectives and study aims

This large, multicenter 2 × 2 factorial cluster-randomized controlled trial aims to reduce ESA use in patients with CAP by optimizing rapid pathogen detection and improving de-escalation rates following negative cultures. The study has two aims:

Aim 1: To determine the impact of comprehensive pneumococcal UAT and rapid viral molecular diagnostic assays on antimicrobial prescribing for CAP.Hypothesis 1: Comprehensive diagnostic testing will allow fewer days of ESA.Aim 2: To compare pharmacist-led de-escalation of empiric antimicrobial therapy following negative cultures to usual care.Hypothesis 2a: Pharmacist-led de-escalation will reduce the number of days of ESA use.Hypothesis 2b: Pharmacist-led de-escalation will be more effective when physicians order UAT/rapid viral testing.

The study proposal was designed following the recommendations of the Standard Protocol Items: Recommendations for Interventional Trials (SPIRIT) and their checklist is included as an Additional file [15].

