### Trial design

We will perform a pragmatic, multicenter 2 × 2 factorial cluster-randomized controlled trial with four arms: rapid diagnostic testing, pharmacist-led de-escalation, rapid diagnostic testing + pharmacist-led de-escalation, and usual care (Table 1).

**Table 1 Tab1:** Two-by-two factorial cluster-randomized controlled trial with four arms

		Pharmacist-led de-escalation	
		Yes	No
Rapid diagnostic testing	Yes	Rapid diagnostic testing + pharmacist-led de-escalation (3 hospitals)	Rapid testing (3 hospitals)
	No	Pharmacist-led de-escalation (3 hospitals)	Usual care (3 hospitals)

We hypothesize there will be an interaction between the two interventions as the diagnostic tests should make it easier for the pharmacist to recommend to clinicians to de-escalate after 48 h. The factorial design allows for comparing the two interventions in combination and individually, against the standard of care. All interventions will be performed at the hospital level to minimize crossover between study arms and allow for consistent care. We will use a cluster-randomized design to minimize cross-contamination and improve the efficiency of intervention administration.

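### The primary test is fixed inconsistently: the analysis section makes a four-group comparison primary, while the hypotheses and the power calculation rest on two 6-versus-6 hospital comparisons

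*Protocol article*

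**What the plan says.** In the protocol article, the section on the data analysis plan describes a linear mixed model for days of ESA, "which will include the treatment arm as a fixed effect and a random-intercept at the randomized hospital level". It then says: "The primary comparison is to compare the duration of exposure to ESA therapy in the four treatment groups". The threshold is general: "We will consider a two-sided *p*-value < 0.05 statistically significant". The interaction is placed outside the primary analysis: "Interaction between the two interventions will be tested as a secondary analysis".

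The objectives section sets two separate hypotheses on the same outcome. Hypothesis 1 is "Comprehensive diagnostic testing will allow fewer days of ESA" and Hypothesis 2a is "Pharmacist-led de-escalation will reduce the number of days of ESA use".

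The sample size section treats these as two calculations. For Aim 1, "we anticipate an average reduction of 0.3 days (SD = 3.5 days) of exposure to ESAs due to rapid diagnostic testing", with 6 hospitals against 6, about 1000 patients per hospital (coefficient of variation 0.4), an intra-cluster correlation (ICC) of 0.001, two-sided alpha 0.05 and 83% power. Aim 2 is also 6 against 6, with a 1-day effect, SD 3, ICC 0.005, two-sided alpha 0.05 and power above 99%.

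The trial design section adds a third view: "The factorial design allows for comparing the two interventions in combination and individually, against the standard of care". The section on interim analyses bases futility stopping on one z-statistic and conditional power for one parameter, without saying which contrast these refer to.

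**The concern.** The sentence that names the primary comparison does not name a contrast. With four arms it could mean one 3-df test of the arm term, three arms against usual care, or the two factorial margins. The hypotheses and the power calculation fit only the margins, and the trial design section also describes comparisons with usual care.

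Two things are at stake. First, a positive conclusion could rest on whichever contrast falls below 0.05, so the error rate of the primary conclusion depends on a choice that the text leaves open. Second, the stated power belongs to only one of the candidates. A reader who takes the analysis section at its word, with three hospitals per arm, is not looking at the test that was powered.

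**Working it through.** **1. Reproduce the stated 83% for Aim 1 (6 versus 6).** Inputs from the sample size section: effect 0.3 days, SD 3.5, ICC 0.001, mean cluster size m = 1000, CV 0.4, 6 hospitals (6000 patients) per side, two-sided 0.05.

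- Design effect: DE = 1 + ((1 + CV²)m − 1) × ICC = 1 + (1160 − 1) × 0.001 = 2.159. The relative-efficiency form gives 2.082.
- SE = SD × √(2 × DE / 6000) = 3.5 × √(2 × 2.159 / 6000) = 0.0939. With DE 2.082 it is 0.0922.
- Noncentrality = 0.3 / SE = 3.20 or 3.25.
- Noncentral t with 10 df (12 hospitals minus 2 groups): power 82.1% or 83.4%.

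The stated 83% therefore reproduces for a 6-versus-6 comparison with the whole 0.05 spent on Aim 1.

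**2. Same inputs, one arm against usual care (3 versus 3).**

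- SE = 3.5 × √(2 × DE / 3000) = 0.1328 or 0.1304.
- Noncentrality = 2.26 or 2.30.
- Noncentral t with 8 df (12 hospitals minus 4 arms): power 51.1% or 52.5%.

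**3. False-positive rate under no effect.** Simulation of four equal, independent arm means (2,000,000 draws), each test at unadjusted two-sided 0.05. The table gives the chance of at least one significant result.

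| Reading of the primary comparison | t, 8 df | Normal |
|---|---|---|
| One global 3-df test of arm | 5.0% | 5.0% |
| Two factorial main effects | 9.4% | 9.7% |
| Three arms versus usual care | 11.7% | 12.5% |
| Both of the last two sets | 15.0% | 16.8% |

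As a check on the second row, two independent tests give 1 − 0.95² = 9.75%. Each main effect taken alone keeps 5%.

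**4. Which reading fits the rest of the article?**

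- *Global test:* allowed by the primary-comparison sentence. It does not answer Hypothesis 1 or 2a, it is not what was powered, and it does not supply the single z-statistic and parameter used for futility.
- *Arms versus usual care:* fits the trial design section. Usual care is also the stated reference group for mortality. It does not match the power calculation.
- *Two margins:* fits the objectives and the power calculation, but not the sentence naming a four-group comparison as primary.

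No single reading fits all the sections.

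**5. Cost of joint control.** Aim 1 at alpha 0.025, 6 versus 6, 10 df: power 70.7% or 72.4%, against 82.1% or 83.4% at 0.05.

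**The case against.** The strongest reply is that the analysis sentence can be read as one test of the arm term, which keeps 5%. That stands as a reading of the sentence, and for that reason no single inflated error rate can be attributed to the plan. It does not remove the inconsistency, because a global test fits neither the hypotheses, nor the power calculation, nor the futility rule.

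A second reply is that the two aims concern different interventions, and that many statisticians would test each main effect of a factorial trial at 0.05 without adjustment. This also stands. The 9–10% is the chance of a false positive on either aim, in either direction. In the direction of benefit only, it is about 4.8–4.9% across the two aims and about 5.9–6.3% for three arms against usual care. Joint control is a choice, not a requirement.

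A third reply is that a hierarchy or alpha split may be in an analysis plan that is not shown. That is fair, and its absence here is not the point. The point is that the article states one primary comparison and powers another.

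A reader might go further and infer that the trial's error rate is simply 9–20% instead of 5%. The article does not support this. The 18–20% end needs all six pairwise tests, and no section plans them for ESA days. Nor does the shared usual-care group add to the inflation: the correlation between the three contrasts lowers the joint error to 12.5%, from 14.3% for three independent tests.

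**Conclusion.** The point holds as an inconsistency in how the primary test is fixed. The analysis section makes a four-group comparison primary, while the objectives and sample size sections set and power two 6-versus-6 comparisons, each at the full 0.05. Depending on the reading, the chance of at least one two-sided false positive is 5%, about 9–10%, about 12% or about 15–17%. Aim 1 power is 82–83% or about 51–52%.

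The error rates assume no effect of either intervention, equal variances of the arm means and unadjusted testing. The power figures take the article's effect size, SD, ICC and cluster-size variation as given, with degrees of freedom from hospital counts and no gain from covariate adjustment. The plan should be corrected, but the article does not show that the trial's error rate is already inflated.

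**What to change.** In the data analysis plan, replace the sentence on the primary comparison. Name the two factorial main effects (testing yes/no and de-escalation yes/no, six hospitals against six) as the only primary tests of days on ESA. Label the arm-versus-usual-care contrasts as secondary, reported with estimates and 95% confidence intervals. The interaction is already secondary. State which of the two contrasts the futility z-statistic refers to.

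Then state the multiplicity position for the two aims. Either is defensible:

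- **Each aim at 0.05 as a separate question.** This keeps the stated power and accepts about 9–10% for a two-sided false positive on either aim.
- **Joint control at 5%, by Holm or a fixed sequence.** Under Holm, Aim 1 may be tested at 0.025, with power about 71–72%. In a sequence that starts with Aim 2, Aim 1 loses less than 1 point of joint power at the stated Aim 2 power above 99%. If 50% compliance halves the Aim 2 effect to 0.5 days, Aim 2 power is about 88–92%, and Aim 1 loses about 7–10 points (0.83 × 0.08 to 0.83 × 0.12).

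Naming the contrasts costs only wording: no change to sites, data or sample size. Joint control, if chosen, costs the power shown.

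### The comparison named primary (four groups of 3 hospitals) is not the one the trial is powered on (6 vs 6 hospitals per aim), so the stated 83% for Aim 1 does not apply to it

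*Protocol article*

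**What the plan says.** **Powering (Sample size and power analysis).** For Aim 1, "we anticipate an average reduction of 0.3 days" with an SD of 3.5. The design is "6 in the rapid diagnostic testing arm and 6 in the control arm", "with an average of 1000 patients per hospital" and a coefficient of variation of 0.4, "at a two-sided alpha of 0.05 and an intra-cluster correlation (ICC) of 0.001", with 83% power. For Aim 2: "For Aim 2, we will compare the six hospitals implementing pharmacist-led antimicrobial de-escalation and the other six hospitals serving as the control group". Both are margins of the 2 × 2 table. The section adds that the interaction is secondary and was not powered.

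**Analysis (Data analysis plan).** The primary outcome goes into a linear mixed model with treatment arm as a fixed effect and a hospital random intercept. Then: "The primary comparison is to compare the duration of exposure to ESA therapy in the four treatment groups". The interaction is again secondary.

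**Layout (Table 1; Participating sites).** Each of the four groups has 3 hospitals.

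**Hypotheses (Objectives and study aims).** There is one hypothesis per intervention (1 and 2a) and a separate one for their joint effect (2b).

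**The concern.** The comparison that is powered and the comparison that is called primary are different estimands on different numbers of hospitals. A factorial trial with 12 clusters relies on using all 12 for each factor. If the primary result comes from single cells, each contrast uses half the hospitals and the stated power no longer describes it.

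The four-group sentence also does not identify which quantity tests Hypothesis 1 and which tests Hypothesis 2a. The futility rule under Interim analyses inherits the gap: it computes conditional power from one current z-statistic, and a cell contrast and a marginal contrast give different values of z for the same data.

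**Working it through.** **Inputs (Sample size and power analysis, Aim 1).** Difference 0.3 days; SD 3.5; ICC 0.001; mean cluster size m = 1000; CV 0.4; two-sided alpha 0.05.

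**Step 1. Design effect (DE).** Two usual ways to allow for unequal cluster sizes:
- Relative efficiency: L = m·ICC / (m·ICC + 1 − ICC) = 1/1.999 = 0.500. RE = 1 − 0.4²·L(1 − L) = 0.96. DE = (1 + 999 × 0.001)/0.96 = 1.999/0.96 = 2.08.
- Inflation by CV: DE = 1 + ((1 + 0.16) × 1000 − 1) × 0.001 = 2.16.

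**Step 2. Reproduce the plan's figure (6 vs 6).** SE = 3.5·√(2·DE/6000) = 0.092 to 0.094. Noncentrality = 0.3/SE = 3.25 to 3.20. Noncentral t on 12 − 2 = 10 df gives 83.4% to 82.1%, which matches the stated 83%. The normal approximation gives 90% to 89% and does not match. The 83% is therefore a cluster-level t calculation on the 6-vs-6 margin.

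**Step 3. The possible readings of the four-group comparison, same inputs.** For one arm vs usual care (3 vs 3), SE = 3.5·√(2·DE/3000) = 0.130 to 0.133 and noncentrality = 2.30 to 2.26.

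| Reading | Reference distribution | Aim 1 power (DE 2.08 to 2.16) |
|---|---|---|
| Rapid testing alone vs usual care, 3 vs 3 | t, 8 df (12 hospitals − 4 arms) | 52.5% to 51.1% |
| Same | t, 4 df (only the six hospitals compared) | 42.0% to 40.8% |
| Same | normal | 63.3% to 61.8% |
| Marginal contrast from the four-arm model, 6 vs 6 | t, 8 df | 81.2% to 79.9% |
| Main effect from a model with two indicators, 6 vs 6 | t, 9 df (12 − 3) | 82.5% to 81.1% |

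No multiplicity adjustment is applied, since the article states none.

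**Step 4. The omnibus reading.** Suppose only rapid testing works. The arm means are then 0, 0.3, 0 and 0.3, and their squared deviations sum to 0.09. The noncentrality is 0.09/(3.5²·DE/3000) = 10.6 to 10.2, and F(3,8) power is 56% to 54%. If de-escalation adds 0.5 days (assumed: 1 day at 50% compliance, effects additive), power is about 99%. That rejection would be driven mainly by de-escalation and would say nothing specific about Hypothesis 1.

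**Step 5. Aim 2 (SD 3, ICC 0.005; CV 0.4 assumed to carry over).** The same formulas give DE 6.13 to 6.80. With the full 1-day difference, even 3 vs 3 on 8 df gives 99%. If 50% compliance dilutes the difference to 0.5 days (an assumption), 6 vs 6 on 10 df gives 91% to 88% and 3 vs 3 on 8 df gives 63% to 59%. The loss for Aim 2 therefore depends on how the compliance statement is read.

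**The case against.** The strongest reply is that the protocol already describes the right comparison. The sample size section says of Aim 2 that six hospitals will be compared with the other six, and Aim 1 is laid out the same way. The hypotheses are one per intervention, and the interaction is secondary, which fits a main-effects primary analysis. A condensed article may also leave exact contrasts to an analysis plan that is not shown here.

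Much of this stands, and it rules out some stronger readings:

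- A reader might infer that the Aim 1 test as written has about 52% power. It does not follow. No pairwise test of the primary outcome is written. Usual care is named as the reference group for mortality, in the Data analysis plan and under Interim analyses, but not for days on ESA. The Trial design section says only that the design permits comparisons with standard of care.
- A reader might infer that a four-level arm model allows only an omnibus test or 3-vs-3 contrasts, so that factorial efficiency is lost. That is wrong. The 6-vs-6 margin is a linear combination of the four arm means from that same model and keeps about 80-81%.
- Lower figures can be produced by adding a Bonferroni correction or by giving Aim 1 the ICC of 0.005. The first is not in the document, and the second belongs to Aim 2.

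The reply does not remove the inconsistency. The article does state a primary comparison, and it differs from the one that was powered. An analysis plan could settle the matter only by overriding one of the two sections.

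**Conclusion.** The inconsistency is established from the text. The 83% belongs to the 6-vs-6 rapid-testing margin and does not describe the four-group comparison named as primary.

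The size of the consequence is conditional. If each arm is tested against usual care, Aim 1 power is about 52% at 8 df, within 41-63% across 4 df to the normal approximation. If a marginal contrast is used, power stays at about 80-83%. An omnibus test would not address either aim's hypothesis.

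These figures rest on the plan's own effect, SD, ICC and cluster sizes, on unadjusted alpha, and on no df being spent on the hospital-level covariates listed in the Data analysis plan. Adjusting for those could lower the df further.

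**What to change.** Replace the four-group sentence in the Data analysis plan. The new text should say:

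- There are two primary tests: the main effect of rapid diagnostic testing (6 vs 6 hospitals, Aim 1) and the main effect of pharmacist-led de-escalation (6 vs 6 hospitals, Aim 2).
- Both come from one mixed model with two binary factor indicators, and each effect is averaged over the levels of the other factor.
- The interaction (Hypothesis 2b) remains secondary, and the four arm means are reported with confidence intervals.

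This changes wording only and adds no hospitals or patients. On 9 df the Aim 1 power is 81-82%, close to the stated 83%.

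The downside is interpretive. The Trial design section expects the two interventions to interact. If that synergy is large, each main effect is an average over two different situations and must be read beside the arm means.

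Adding stratum to the model is a separate decision and is not needed here. It would leave 12 − 1 − 2 − 2 = 7 df and about 78-80% power for Aim 1, before any variance reduction from stratification.
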